### Study population

The inclusion criteria specific to this study comprise the ability to give informed consent, the patient’s wish to receive IN DAM during HAT participation and a medical indication for IN DAM. Swiss HAT centres additionally recommend a specialist examination of the nose and nasal cavities, but this is not mandatory for patients.

All other inclusion criteria are not specific to the study but correspond to the inclusion criteria of Swiss HAT and the guidelines for DAM treatment defined by the Swiss HAT institutions [29]. To be eligible for HAT in Switzerland, patients must be at least 18 years old, have a history of severe opioid dependence of more than 2 years, have a history of at least two unsuccessful conventional treatment attempts for opioid dependence (e.g., continued engagement in high-risk use behaviour) and have documented social or health problems as a result of opioid dependence [29]. We expect that most participants will be in HAT with other routes of administration prior to study inclusion.

Patient will not be eligible to participate in this study if they have severe cognitive impairment (e.g., dementia or substance-induced impairments) or insufficient language proficiency, rendering the reliable completion of the self-report forms/questionnaires impossible.

### Study procedures

Participants will be recruited only after the decision for nasal DAM is made by the participants and the responsible physician independently from study procedures. Patients will be informed that study participation is voluntary, that they may withdraw from the study at any time and that withdrawal of consent will not affect their subsequent medical assistance and treatment. Patients will be given at least a day to consider participation in the study. Study procedures comprises of assessments with questionnaires and structured interviews at baseline, 4, 52, 104, 156 weeks, and of a duration around one hour each. These are described below and in Table 1.

**Table 1 Tab1:** Study assessments

*Study periods*	*Assessment 1 (Baseline)*	*Assessment 2*	*Assessments 3, 4 and 5*
*Time (weeks)*	*0*	*4*	*52, 104, 156*
*Inclusion/Exclusion Criteria*	*X*		
*Written Informed Consent*	*X*		
*Patient characteristics*	*X*		
*Medical History*	*X*		
*Retention*^*a*^	*X*	*X*	*X*
*Opioid agonist prescription*^*a*^	*X*	*X*	*X*
*Treatment adherence*^*a*^	*X*	*X*	*X*
*Frequency of visits*^*a*^	*X*	*X*	*X*
*Treatment Outcomes Profile (TOP)*^*b*^	*X*	*X*	*X*
*Health section of Opiate Treatment Index (OTI)*^*b*^*, including nose-related problems*	*X*	*X*	*X*
*Symptom-Checklist 27 (SCL-27)*^*b*^	*X*	*X*	*X*
*Adverse Events*^*b*^	*X*	*X*	*X*
*Opioid Agonist Scale*^*1,c*^	*X*	*X*	
*VAS Subjective effects*^*2,c*^	*X*	*X*	
*VAS Craving*^*c*^	*X*	*X*	*X*
*VAS Satisfaction*^*c*^	*X*	*X*	*X*

^1^20–30 min after DAM application

^2^10 min after DAM application

^a^Used to assess feasibility of IN DAM

^b^Used to assess safety of IN DAM

^c^Used to assess acceptability of IN DAM

Patients will remain in the study if they change route of administration of DAM and will continue assessments even if they no longer receive IN DAM until study completion after three years. Patients who switch from IN DAM to another DAM route of administration and subsequently switch back to IN DAM will be allowed to do so, as it is an observational study of clinical procedures. Short-term switches to other forms of DAM or OAT due to external circumstances such as vacations abroad (where DAM cannot be taken), illness, hospitalisations or similar will be considered as continuous IN treatment, as the basic prescription will not change. If a patient switches to another route of DAM administration as per prescription, this will be systematically assessed, and a change back to IN DAM as well.

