Currently available routes of DAM administration (IV and oral) are also increasingly insufficient due to changing patterns of substance use. In Switzerland and the EU, intranasal use is increasing, while inhalation and injection are decreasing [13, 14]. Given the current treatment options, individuals who are using opioids intranasally and entering HAT are prescribed oral DAM. A prescription of injectable DAM for non-injecting patients would ethically be unacceptable due to the higher risks associated with this route of administration. However, as previously mentioned, oral DAM has a much slower onset and less subjective effects. Hence, it often has limited efficiency in this patient group and may lead to treatment drop-out, ongoing illicit substance use, diversion of DAM tablets and delinquency. Some patients that would otherwise qualify for HAT and mainly use illicit opioids intranasally may even be discouraged from entering HAT for these aforementioned reasons [4].

In order to address these clinical gaps, minimise harm, and improve treatment outcomes, a novel route of DAM administration (intranasal; IN) has been developed as an alternative to IV or oral DAM for patients in HAT. It has a similar onset of effect as IM administration and is thus likely to produce the desired “rush” [15–17]. Currently prescribed off-label in a small number of HAT patients, it seems to be associated with less adverse effects than IV, IM or SC injection and has been suggested as a harm reduction measure to reduce HCV infection rates [18, 19]. Intranasal HAT (n-HAT) was first described in a case-series and was suggested as an important risk-reduced rapid-onset alternative to other forms of HAT [20]. In a recently published case-report, IN DAM administration improved treatment adherence and health outcomes in a patient who craved the fast onset of effect of DAM but was unable to inject intravenously [19]. Similarly, patients in HAT comparing a one-off administration of IN DAM with IV DAM reported advantages for IN administration such as ease and convenience of use, avoidance of needle hazards, and reduced stigma [15]. Finally, overdose from nasal use occurs much less often than from IV use [21].

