## Methods

### Study design

The study is designed as an exploratory prospective multicentre clinical cohort study. Every HAT centre in Switzerland was invited to participate and 18 confirmed their participation. Given that there are 23 specialist outpatient centres offering HAT in Switzerland, this study is representative of the treatment system [29]. Within this treatment system, these outpatient centres provide HAT to around 1600 patients, which has been relatively constant within the last two decades [30]. Enrolled participants will switch from oral or injectable DAM (treatment as usual arm) to intranasal DAM. Follow-up will occur over three years, with assessments at baseline (t0), and after 4 (t4), 52 (t52), 104 (t104) and 156 (t156) weeks. These timepoints are standard follow-up periods when measuring retention in OAT [31]. Specifically, the first 4 weeks in OAT are particularly important as the risk of mortality is elevated when compared with the remainder of time receiving OAT [32]. Long-term retention in HAT has also been studied at similar time points (e.g., 2 years in Germany, 2 years in Spain, 4 years in the Netherlands) [33–35].

Participants in n-HAT will receive Diaphin^®^ IV 100 mg/ml (DiaMo Narcotics, Thun), approved in Switzerland for IV treatment of OUD in the HAT setting. It will be administered into the nostrils with a mucosal atomisation device (Fig. 1). Atomisers are personalised, disinfected following each administration and replaced every 7 days. Just like conventional treatment with IV and IM DAM, long-acting oral opioids such as methadone or and slow-release oral morphine can be used as additional medication in order to prevent withdrawal. Participants will also be allowed to combine nasal with oral, IV and IM DAM. The dosing of IN DAM and of DAM through other routes of administration will remain an individual decision of patients and prescriber. Therefore, patients will not receive the same dosification, but rather receive an IN DAM dosification that align with their needs. There is no limitation on concomitant opioid and/or non-opioid medication to be prescribed. This study design is meant to be as comparable to the current Swiss HAT setting as possible.

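### Eligibility and recruitment rules do not tie t0 to the first intranasal dose, so patients already on intranasal DAM could enter, with retention counted late and no clean pre-switch baseline

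*Protocol article*

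**What the plan says.** Study design presents the cohort as people who change route after enrolment: "Enrolled participants will switch from oral or injectable DAM (treatment as usual arm) to intranasal DAM". The Abstract, Sample size and power calculation, Discussion, and Strengths and limitations use similar language of being offered, trying, being switched to or being started on IN DAM.

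The rules that a site would apply are in two other sections. Study population lists, besides capacity to consent, "the patient’s wish to receive IN DAM during HAT participation and a medical indication for IN DAM". It then adds: "All other inclusion criteria are not specific to the study but correspond to the inclusion criteria of Swiss HAT". The exclusions concern only cognition and language ("Patient will not be eligible to participate in this study if they have severe cognitive impairment" and the language clause that follows). Study procedures says "Participants will be recruited only after the decision for nasal DAM is made by the participants and the responsible physician independently from study procedures", and "Patients will be given at least a day to consider participation in the study".

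The Introduction says of IN DAM: "Currently prescribed off-label in a small number of HAT patients".

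Under Primary outcome assessment, a participant is retained if IN DAM is prescribed at the assessment. Table 1 counts assessments at weeks 4, 52, 104 and 156 from baseline.

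**The concern.** Taken literally, the eligibility list admits someone who has used IN DAM for months, and also someone who started between the clinical decision and consent. No sentence orders t0 and the first IN DAM dose.

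Two things depend on that order.

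- **The primary outcome.** Retention is a single-arm figure with no concurrent control, so a late start of the clock cannot cancel out. A person who tries the spray and stops before consent is never counted, while one who continues is. Study design justifies the week-4 assessment by the particular importance of the first four weeks of treatment, and that reasoning needs a clock that starts with treatment.
- **The before-after hypotheses.** Study objectives and hypotheses expects fewer prescribed injections and less illicit opioid use. Both need a value from before IN DAM. Table 1 assigns the t0 subjective effects and satisfaction to acceptability of IN DAM, and Secondary outcome assessment does not name the route used before the t0 effect ratings. The role of t0 is therefore open to two readings.

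**Working it through.** The article gives no retention calculation to reproduce. It gives an expected accrual of 100 to 200 and a preliminary 4-week retention of over 90%, without numerator or denominator. The check is therefore a comparison of the text, followed by an illustration.

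**Text.**

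| Question | Intent (Abstract, Study design, Sample size, Discussion, Limitations) | Rule (Study population, Study procedures) |
|---|---|---|
| May current IN DAM users enter? | Implicitly no | Not excluded |
| Is t0 at or before the first IN DAM dose? | Implicitly yes | Not stated |
| When does recruitment occur? | Before the switch | After the decision, with at least a day to consider and no upper limit |

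The intended population is clear. The rule that would secure it is absent.

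**Illustration (all inputs assumed).** Let time to leaving IN DAM follow a Weibull curve, S(t) = exp(−λt^k), with t in weeks. New starters are retained with probability S(t). Patients with prior use a are retained with probability S(t+a)/S(a). With a share q established, observed retention is (1−q)·S(t) + q·S(t+a)/S(a).

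Worked case: k = 0.5, S(4) = 0.90, a = 52, q = 0.10, at week 52.

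- λ = −ln(0.90)/4^0.5 = 0.0527
- New starters: exp(−0.0527 × 7.211) = 0.684
- Established: exp(−0.0527 × (10.198 − 7.211)) = 0.854
- Observed: 0.9 × 0.684 + 0.1 × 0.854 = 0.701, a shift of 1.7 points

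Upward shift, in percentage points, over k = 0.5 and 0.7, S(4) = 0.80 and 0.90, a = 12 and 52 weeks:

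| Share established | Week 4 | Week 52 | Week 156 |
|---|---|---|---|
| 10% | 0.5 to 1.7 | 0.7 to 2.7 | 0.2 to 2.0 |
| 50% | 2.5 to 8.5 | 3.6 to 13.5 | 1.1 to 10.0 |

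With a constant hazard (k = 1) every shift is 0. The 50% row is an outer case, and the off-label group is described only as small. Ten per cent of 100 to 200 would be 10 to 20 people.

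**Short delay (assumed).** Suppose 10% stop in week 1 and 5% of the remainder over weeks 2 to 4. Retention at 4 weeks from first dose is 0.90 × 0.95 = 85.5%. After week 1 the weekly hazard is −ln(0.95)/3 = 0.0171, so a cohort that all enrolled one week late would show exp(−4 × 0.0171) = 93.4%, a shift of 7.9 points. If only 10% of the cohort enrolled a week late, the shift would be about 0.1 × 7.9 = 0.8 points.

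**Scale.** The 95% half-width, 1.96 × √(p(1−p)/n), is 5.9 points (n = 100) or 4.2 (n = 200) at p = 0.90, and 9.8 or 6.9 at p = 0.50.

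**The case against.** A reader might infer that the primary result is inflated, that the preliminary figure of over 90% is a product of timing, or that the study has no pre-switch baseline. The documents do not support any of these.

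- **Intent.** Five parts of the article describe people moving to IN DAM. Someone stable on it cannot switch to it or try it out. The recruitment sentence concerns the decision, not dosing already begun, and one day to consider does not imply a week's delay. This stands: the article does not show that any established user entered.
- **Direction.** Overstatement needs a falling hazard of stopping, which is plausible but not documented. Anyone who consents and never starts would count as not retained, which pulls the figure down. Nor is the effect necessarily largest at week 4: in most of the settings above it is larger at week 52.
- **Size.** The 93.4% requires the whole cohort to enrol a week late, which nothing suggests. At 10% established, the shift is below the sampling half-width. This stands, although sampling error shrinks with n and this bias does not.
- **Baseline.** It is affected only for those already on IN DAM at t0. The Treatment Outcomes Profile, the health section of the Opiate Treatment Index and the chart record of prescriptions and routes all look back four weeks. A very recent starter therefore keeps some pre-switch information, and current users can be identified.
- **Condensation.** An article may leave visit windows to the full protocol. Here, however, the criteria are set out rather than deferred, and they admit people whom the design text does not describe. Statements of intent are not a rule that a site can apply.
- **Disclosure.** The limitations acknowledge that participants were already interested in IN DAM. That concerns generalisability, not where the clock starts.

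**Conclusion.** The switch design and the eligibility and recruitment rules do not match. As written, the rules allow entry after IN DAM has begun, and the article says such patients exist in the source population. For those individuals retention is counted late and t0 is not a clean pre-switch value. For the rest of the cohort neither problem arises.

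The size cannot be derived from the article. It is zero if nobody starts before t0 or if the stopping hazard is constant. With 10% established users and a falling hazard it is about 0.5 to 3 points at weeks 4 and 52, and 0.2 to 2.0 points at week 156. These ranges rest on the assumed Weibull shapes, 4-week retention of 80% to 90% and prior use of 12 to 52 weeks.

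The study is exploratory and sets no retention threshold, so this falls short of a defect that must be resolved before the study can be interpreted. It goes beyond wording, though, because it fixes the time origin of the primary outcome.

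**What to change.** Reconcile Study design, Study population and Study procedures, as a matter of assessment timing and analysis only. Prescribing stays independent of the study.

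- State that the t0 assessment takes place before or on the day of the first prescribed IN DAM dose.
- Take the date of first IN DAM prescription from the chart for every participant, including those already enrolled, and count retention from it.
- Base the primary retention estimate and all comparisons with t0 on new starters, defined as having no IN DAM prescription before t0. This definition also covers people who enter HAT directly on the nasal route.
- Report anyone already on IN DAM at consent separately, with time counted from the actual start and delayed entry at consent.
- Give the number who consent but never start, since they have no start date.

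The cost is one sentence in the criteria and one chart date per participant. The primary denominator becomes slightly smaller, and the retention figure may be less favourable.

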### Primary outcome assessment

The primary outcome is retention in treatment with IN DAM after 4 weeks, 52 weeks, 104 weeks and 156 weeks. Success on primary outcome is defined as participants receiving IN DAM at each follow-up. Therefore, we will assess the prescription at the time point of assessment, and patients receiving IN DAM at the time point of assessment will be considered retained. However, since patient may switch to another route of DAM administration and then switch back to IN DAM within the follow-up periods, we will also separately calculate continuous IN DAM retention from “intermittent” IN DAM retention for patients changing and returning to and from other routes of DAM, and will assess time spent in prescription of IN DAM compared to other routes of administration.

### Secondary outcome assessment

Opioid agonist prescriptions including substance, galenics, dose and route of administration in the past 4 weeks will be assessed using patient’s the medical charts at each time point (t0, t4, t52, t104, t156).

Adherence to treatment and frequency of visits in the past 4 weeks will be assessed using the recorded scheduled and realised dispensings in the patient’s medical charts at each time point (t0, t4, t52, t104, t156).

Illicit substance use, delinquency, health and social functioning and quality of life will be assessed by the Treatment Outcome Profile (TOP) at each time point (t0, t4, t52, t104, t156). The TOP is a 20-item instrument which assesses substance use, injecting risk behaviour, and crime by self-report in the past 4 weeks [38]. Quality of life and social functioning will be assessed using the proposed 0-to-20-point scale of the TOP at each time point (t0, t4, t52, t104, t156).

Opioid craving in the past 7 days will be measured by visual analogue scales (VAS) at each time point (t0, t4, t52, t104, t156). Craving for alcohol, benzodiazepines and cocaine will be measured likewise. Acceptability of nasal DAM will be assessed by VAS on satisfaction with the different routes of administrations in DAM. Additionally, questions on the willingness to continue with the current prescription will be asked.

Subjective DAM effects will be measured by visual analogue scales (VAS) twice (t0 and t4), 10 min after DAM application. The VAS presents the participant a rating scale which represents the spectrum of “opioid high”, heroin-typical effects, good effects, bad effects, pleasure and feeling unwell: the left end indicates “none” while the right end indicates “extreme” effects.

Furthermore, subjective effects of opioids will be assessed using the self-reported German version of the Opioid Agonist Scale at baseline and 4 week follow-up point (t0 and t4) [39]. Between 20 and 30 min after DAM administration, participants will rate the extent to which they experienced each of 16 morphine-like symptoms on a five-point scale from “not at all” to “extremely”.

Physical health in the past 4 weeks will be assessed using the health section of the Opiate Treatment Index (OTI) at each time point (t0, t4, t52, t104, t156) [40]. Only the health section of the OTI will be used; the physical health section of the OTI is composed of items addressing signs and symptoms in major organ systems and injection-related health problems. An additional self-designed section regarding nose-related problems will also be included, inquiring for stuffed and/or runny nose, nasal burning or itching, nasal pain, nasal bleeding, alterations of smell or other problems.

Self-reported mental health symptoms in the last 7 days will be assessed using the Symptom-Checklist 27 (SCL-27) at each time point (t0, t4, t52, t104, t156). The SCL-27 is the short German version of the 90-item SCL-90 [41]. The SCL-27 is a commonly used reliable and valid instrument, consisting of six subscales and a general score.

Although this is an observational study and not a randomised controlled trial and the decision on which routes of administration will be used for DAM remains with clinicians and patients, we will assess safety with several different measures. First, study physicians will report any serious adverse events (SAEs) followed by immediate information of all study centres. Second, we will assess physical health and especially nasal health with the health section of the OTI and self-designed questions on nasal symptoms. Third, we will assess risk behaviour such as number of injection events inside and outside of treatment. AEs and SAEs are defined in the “Safety” section.

### Sample size and power calculation

We aim to include all patients willing to participate in the study. As this is an exploratory observational study, it is not possible at this point to exactly predetermine the final sample size, as it depends on the number of patients interested in and qualifying for n-HAT and consenting to participation in this clinical observation. We think that over the planned accrual time of two years, it is realistic to include between 100 and 200 participants who will try out IN DAM.

### Safety

Safety will be assessed by the appearance of adverse events (AEs) and serious adverse events (SAEs). AEs and SAEs will be monitored throughout the study. A serious event is defined as any adverse event where it cannot be excluded, that the event is attributable to the IN administration of DAM or the collection of health-related personal data, and which: (a) requires inpatient treatment or extends a current hospital stay, (b) results in permanent or significant incapacity or disability, or (c) is life-threatening or results in death.

If a serious adverse event related to study procedures occurs, the research project will be interrupted, and the Ethics Committee notified. If an event related to IN DAM administration is reported, all Swiss HAT centres will be informed. The decision whether ongoing IN DAM treatments are continued or not, however, will then be made independently of the study by the responsible physicians.

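### The serious-event definition makes possible attribution to IN DAM or data collection a condition of seriousness, so the SAE count is not all-cause and cannot be compared between time on and off IN DAM

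*Protocol article*

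**What the plan says.** The Safety section of the protocol article defines a serious event as "any adverse event where it cannot be excluded, that the event is attributable to the IN administration of DAM" and continues "or the collection of health-related personal data, and which: (a) requires inpatient treatment or extends a current hospital stay". Criterion (b) covers lasting or significant disability, and (c) covers an event that "is life-threatening or results in death".

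The same section bases safety on adverse events as well as serious ones and states that "AEs and SAEs will be monitored throughout the study". It attaches no causality condition to adverse events.

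The Secondary outcome assessment section promises that "study physicians will report any serious adverse events (SAEs) followed by immediate information of all study centres" and says that both AEs and SAEs are defined under Safety. Only the serious event is defined there. That section and footnote b of Table 1 also list safety measures that need no attribution: the OTI health section with nasal items, SCL-27, TOP, adverse events and injection events.

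Two features of the design matter for attribution. The Study design section states that "Participants will also be allowed to combine nasal with oral, IV and IM DAM", with no restriction on other medication. Under Study procedures, participants who change route stay in the study and keep being assessed up to three years.

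**The concern.** Seriousness describes the outcome of an event, and relatedness is a judgement about its cause. The definition joins the two, so the judgement decides whether an event enters the count at all. A reader of the final report would naturally take the number of SAEs as the number of hospitalisations, life-threatening events and deaths in the cohort. Under this definition it is the number for which a physician did not rule out a link to IN DAM or to data collection.

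Safety is one of the three stated aims and part of the third hypothesis. A low SAE count could mean few serious events, or many that were judged unrelated, and the count alone cannot tell these apart. There is also no concurrent comparator, so follow-up after stopping IN DAM is the nearest internal reference. The definition makes the SAE count unusable for that comparison.

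**Working it through.** The documents give no formula or safety event rate on this point, so there is no figure to reproduce. The check sets the sections side by side.

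**1. What the definition admits.** The causality condition and criteria (a) to (c) are joined by a conjunction, so both must hold.

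| Meets (a), (b) or (c)? | Attribution to IN DAM or data collection excluded? | Status |
|---|---|---|
| Yes | No | SAE |
| Yes | Yes | Not an SAE; possibly an AE, with no marker of seriousness |
| No | Either | Not an SAE; possibly an AE |

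The second row is the problem. Death falls under (c), so it is subject to the same condition.

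**2. Size of the effect.** Let *p* be the share of events meeting (a) to (c) for which attribution is not excluded.

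counted SAEs = *p* × all-cause serious events; share lost = 1 − *p*

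The documents give neither *p* nor the all-cause rate. The share lost can lie anywhere from none (*p* = 1) to nearly all (*p* close to 0).

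**3. Time on and off IN DAM.** Write *p*(on) and *p*(off) for the two kinds of follow-up time.

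observed rate ratio (on/off) = true all-cause rate ratio × *p*(on) / *p*(off)

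While a participant takes IN DAM, often with other routes, a link will often be impossible to rule out, so *p*(on) may be high. Well after IN DAM has stopped, a link can usually be ruled out, so *p*(off) should be low. The ratio is then distorted by the definition itself, and in a direction that would make time on IN DAM look worse. The absolute count, by contrast, is too low in both periods unless *p* = 1.

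**4. Whether other planned data fill the gap.**
- TOP and the OTI health section look back 4 weeks, and SCL-27 looks back 7 days. With follow-up visits at weeks 4, 52, 104 and 156, the longer windows cover 4 × 4 = 16 of 156 weeks, and 16/156 = 10.3%. Self-report cannot record a death.
- Adverse events are monitored throughout, so unrelated serious events may be captured there. The article gives no AE definition and no way to pick out the serious ones.
- Under Discontinuation, dropouts and their reasons are recorded. A death ends HAT and should appear there, but reasons are classed under acceptability.

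**5. Whether the denominator exists.** The Primary outcome assessment section already plans to measure time spent on IN DAM and on other routes, and Study procedures has route changes assessed systematically. Person-time on and off IN DAM therefore needs no new data.

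**The case against.** The strongest case on the other side has four parts.

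*Nothing says these events go unrecorded.* Correct. A reader might infer that all-cause deaths, overdoses and hospitalisations disappear from the study. The text does not support that: AEs are followed throughout with no stated causality filter. What is lost is the label that would let serious events be counted.

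*The threshold is inclusive.* An event leaves the category only if attribution is positively excluded. Combined routes make exclusion harder and so favour counting the event. This stands for time on IN DAM, and it defeats any argument that mixed routes by themselves cause under-counting. It does not help for time after stopping, and it is what makes the two periods differ.

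*Safety does not rest on SAEs alone.* Correct. A reader might infer that the whole safety objective hangs on a causality judgement. The OTI and nasal items, SCL-27, TOP, AEs and injection events need none. The point is confined to the SAE component.

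*An article condenses.* The absence of causality guidance or a relatedness field is no finding, because the full protocol may contain them. The definition itself is printed, however, and so is the pointer to an AE definition that the Safety section does not supply. It would be too strong to call the promise to report any SAE a contradiction, since that passage defers to the Safety section for what an SAE is.

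**Conclusion.** The point holds for the SAE component of the safety assessment. As written, that component counts possibly related serious events only, varies with how physicians attribute events, and cannot be compared between time on and off IN DAM. The article names no all-cause count of serious events or deaths.

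The size cannot be given: the documents contain neither a serious-event rate nor the share judged unrelated, and no figure should be attached to the under-count. The documents also say nothing about how serious events are counted in other HAT cohorts, so no claim about external comparability is made.

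The on/off conclusion assumes that attribution to IN DAM is easier to exclude after IN DAM has stopped. That follows from the definition but is not stated in the article. Even with an all-cause count, an on/off comparison remains observational, because those who stop IN DAM may differ from those who continue. The change is worth making before analysis, because unrelated serious events are hard to identify in retrospect if nothing marked them at the time.

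**What to change.** For the analysis:

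- Classify an event as serious by criteria (a) to (c) alone, whatever its cause.
- Record relatedness in a separate field: IN DAM, other route of DAM, illicit use, study procedures, unrelated.
- Report all-cause serious events and deaths beside the possibly related subset, each per person-time on and off IN DAM. State how short switches are assigned; Study procedures already treats those due to external circumstances as continuous IN treatment.
- Supply the AE definition, or correct the cross-reference to it.

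Leave the notification, information and interruption rules in the Safety and Secondary outcome assessment sections tied to relatedness as they now stand. Ethics-committee notification and interruption follow a serious event related to study procedures, while an event related to IN DAM leads to informing the HAT centres. Because immediate information of study centres is tied to the term SAE, the analysis category should carry its own name, so that widening the count does not widen that duty.

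The cost is one added field and slightly more event recording, with no new procedure or visit. The change does not recover events after a participant leaves HAT, because dropouts are not followed up under either definition.
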